# Efficacy of manual acupuncture, electro-acupuncture, and warm acupuncture for knee osteoarthritis: study protocol for a randomized controlled trial

**DOI:** 10.1186/s13063-022-06653-7

**Published:** 2022-08-20

**Keywords:** Knee osteoarthritis, Manual acupuncture, Electro-acupuncture, Warm acupuncture, Randomized controlled trial

## Abstract

**Background:**

Acupuncture is one of the most popular complementary and alternative treatments for knee osteoarthritis (KOA). There are many methods of acupuncture in the treatment of KOA, and the effects are different. According to our clinical observations and researches, it is found that manual acupuncture (MA), electro-acupuncture (EA), and warm acupuncture (WA) are used more frequently in the treatment of KOA, and the curative effects are satisfactory. However, there is currently a lack of efficacy comparison of efficacy between different acupuncture treatments, as well as a lack of standardized clinical research on the acupuncture treatment of KOA. Therefore, we will carry out a high-quality clinical randomized controlled trial to research the effect laws of MA, EA, and WA on KOA.

**Methods/design:**

A total of 200 eligible participants with KOA will be randomly assigned to group A, B, C, or D in a ratio of 1:1:1:1. Patients in group A will receive MA, while those in group B, group C, and group D will be treated with EA, WA, and sham acupuncture (SA), respectively. Patients will be treated with acupuncture once a day, 30 min per session, 5 sessions per week for 4 weeks. The primary outcome is the change of Western Ontario and McMaster Universities Osteoarthritis Index (WOMAC) at week 4. The secondary outcomes include WOMAC, visual analog scale (VAS), Arthritis Quality of Life Measurement Scale Simplified Scale (AIMS2-SF), Beck Anxiety Inventory (BAI), Beck Depression Inventory (BDI), and Credibility/Expectancy Questionnaire. The evaluation will be performed at baseline and weeks 4, 8, and 12 respectively after randomization.

**Discussion:**

This is a randomized controlled trial. We will observe the clinical effect of MA, EA, and WA on KOA to research the effect laws of these three acupuncture treatments on KOA and set up standardized treatment programs for acupuncture for KOA.

**Trial registration:**

China Clinical Trials Registry ChiCTR2100049526. Registered on August 2, 2021

**Supplementary Information:**

The online version contains supplementary material available at 10.1186/s13063-022-06653-7.

## Introduction

Knee osteoarthritis (KOA) is a common chronic progressive disease characterized by the degeneration and secondary bone hyperplasia of the knee articular cartilage. Pain and functional limitation are the primary clinical symptoms of KOA that prevent patients from engaging in their usual activities [1]. According to an epidemiological survey in the USA, about 240 people are diagnosed with KOA every year in every 100,000 people. Among people over 45 years old, the prevalence of KOA in males is about 6–13% and in females is about 7–19%, and females have a 45% higher risk than males [2]. The overall KOA prevalence in Spain, Italy, Greece, and Norway is 12.2%, 5.4%, 6.0%, and 7.1%, respectively [3]. In China, the incidence of KOA is 8.1%, of which 5.7% in men and 10.3% in women [4]. As a high-prevalence chronic joint disease [5], KOA has become one of the leading causes of disability in the world and brings an increasing social and economic burden [6]. With the aging population, KOA is now a major health risk for middle-aged and elderly people [7].

Patients with KOA often present joint pain, stiffness, and limited mobility. However, knee pain largely affects KOA patients’ quality of life and is the major reason patients seek medical help and advice [5]. The aim of KOA treatment can provide symptomatic pain relief and improve knee function and the quality of life [8]. Currently, drug therapy and surgical treatment are the two major interventions for KOA. Drug therapy takes effect very soon, but it always comes with certain side effects and gastrointestinal adverse reactions. Surgical treatment tends to be expensive and is often accompanied by contraindications and complications, limiting its wide application.

Considering the increasing burden of knee surgery and the side effects of conventional medications, an increasing number of patients with KOA are likely to choose complementary and alternative treatments [9]. As one of the most popular complementary and alternative treatments [10], acupuncture has been used to treat osteoarthritis disorders in China since ancient times [11], and systematic reviews of randomized controlled trials (RCTs) suggested the benefits of acupuncture for KOA [12, 13]. Moreover, many guidelines for the diagnosis and treatment of KOA also recommend using acupuncture in the treatment of KOA [14, 15]. However, there are many methods to treat KOA with acupuncture, and the curative effects are also different. Based on our clinical observations and researches, it is found that manual acupuncture (MA), electro-acupuncture (EA), and warm acupuncture (WA) were used more frequently in the treatment of KOA and the treatment effects were satisfactory [16, 17]. Therefore, we will carry out a high-quality clinical randomized controlled trial to research the effect laws of these three acupuncture treatments on KOA.

## Methods and analysis

### Study design

This is a randomized controlled trial (RCT) that aims to compare the effect of MA, EA, and WA acupuncture methods in the treatment of KOA. This trial has been approved by the ethical committees of the First Affiliated Hospital of Henan University of Traditional Chinese Medicine (No: 2021HL-158) and registered in the Chinese Clinical Trial Registry, ChiCTR2100049526. The protocol will be reported following Standard Protocol Items: Recommendations for Interventional Trials (SPIRIT) reporting guidelines [18] (Additional file 1). A total of 200 patients diagnosed with KOA according to the American College of Rheumatology clinical criteria will be recruited [19]. After informed consent acquisition, all patients will be randomly assigned to group A (MA group), group B (EA group), group C (WA group), and group D (SA group) based on the ratio of 1:1:1:1, to receive treatment. The treatment procedure will include 20 sessions of treatments in total from baseline to week 4 and 2 times of follow-ups on week 8 and week 12 respectively. Outcome measurements will be assessed according to the following time schedule. Figure 1 shows the study design in the flowchart, and Table 1 illustrates the time schedule of enrolment, interventions, assessments, and visits of participants.

**Fig. 1 Fig1:**
[figure not shown]
Flowchart of trial procedures. Flowchart of the trial. KOA knee osteoarthritis, WOMAC Western Ontario and McMaster Universities Osteoarthritis Index, AIMS2-SF Arthritis Quality of Life Measurement Scale Simplified Scale, BAI Beck Anxiety Inventory, BDI Beck Depression Inventory, VAS visual analog scale

**Table 1 Tab1:** Schedule for enrollment, intervention, and assessments during the study period

Timepoint	Enrollment allocation		Treatment period				Follow-up	
	−1 week	0 week	1 week	2 week	3 week	4 week	8 week	12 week
**Enrolment**								
Eligibility screen	X							
Baseline	X							
Informed consent	X							
Randomization	X							
Medical history	X							
Merger disease	X							
Allocation		X						
**Interventions**								
Group A			X	X	X	X	X	X
Group B			X	X	X	X	X	X
Group C			X	X	X	X	X	X
Group D			X	X	X	X	X	X
**Assessments**								
WOMAC		X				X	X	X
VAS		X				X	X	X
AIMF2-SF		X				X	X	X
BAI		X				X	X	X
BDI		X				X	X	X
CEQ		X						
Adverse events		X	X	X	X	X	X	X

Qualification screening and informed consent will be completed before the assignment. After allocation, each patient will be treated within 4 weeks. The evaluation will be performed at baseline and weeks 4, 8, and 12 respectively after randomization. Adverse events will be recorded on the case report form at any time during treatment

### Study setting and recruitment

The study will be carried out at the First Affiliated Hospital of Henan University of Traditional Chinese Medicine. Two hundred patients with KOA will be recruited via two schemes. The first is to recruit patients in the outpatient and inpatient departments from the First Affiliated Hospital of Henan University of Traditional Chinese Medicine. Moreover, potential patients in local communities and out-hospital clinics will be recruited by advertisements through posters, leaflets, newspapers, and so on. The recruitment information will provide a telephone number so that potential patients can be able to contact the researchers. People willing to participate in the study will be invited to contact the clinical research coordinator (CRC) by telephone. The CRC will perform a preliminary screening of people for inclusion and exclusion criteria and then, if appropriate, schedule a face-to-face baseline visit with a senior specialist in physical and rehabilitation medicine. All eligible patients will provide written informed consent. The CRC will discuss the study in detail (i.e., the study purpose, procedures, and time commitment, as well as the potential risks and benefits associated with participation in the study) with potential patients and obtain written informed consent. The confidentiality of patient records will be protected. At the time of enrolment, each patient will be assigned a unique randomization number, which is the only direct identifier included on all case report forms.

### Participants

#### Inclusion criteria

Participants who meet all of the following requirements will be considered for inclusion: (1) male or female, aged 45–75 years; (2) diagnosed with KOA according to the American College of Rheumatology (ACR) criteria; (3) radiologic confirmation of KOA [20] (Kellgren–Lawrence gradesIto III); (4) the average daily pain scare over 40 points (on a 0- to 100-point scale); (5) symptoms have been present for more than 6 months without redness, swelling, or heat; and (6) signed informed consent.

#### Exclusion criteria

Patients who meet any of the following criteria will be excluded from the trial: (1) are unable to walk; (2) have a serious infection of the knee; (3) have suspected tears in any ligaments or menisci or acute inflammation of the synovial capsule; (4) have a history of trauma, ligament damage, fracture, or surgery on the knee(s) within 6 months, causing pain or functional problems (history of knee replacement will be excluded); (5) have a history of local tumor/malignancy at the knee; (6) have physical or laboratory findings indicating infection, presence of autoimmune disease, or inflammatory arthritis; (7) have knee pain caused by radiculopathy/herniation of an intervertebral disc; (8) have end-stage diseases or other suspected severe conditions such as deep vein thrombosis of the lower limb, edema related to cancer or cancer treatment, severe blood coagulation disorders, uncontrolled systemic arterial hypertension, and severe diabetes; (9) have a history of prolotherapy, hyaluronic acid injections, or corticosteroid injections within 3 months; (10) have received acupuncture, electro-acupuncture, Tui-na therapy, massage, or physiotherapy 8 weeks prior to enrolment in the trial; (11) have severe pain in other regions; (12) have severe mental disorder(s); (13) are oversensitive to needles; and (14) are insensitive to pain due to advanced diabetes, neuropathy, or use of strong painkillers.

### Discontinuation criteria and modification

During the trial period, patients with KOA who meet the following criteria will be excluded from the study: (1) protocol violation such as taking analgesic without permission or receiving additional treatment that may interfere with the efficacy of acupuncture, (2) withdrawal of consent for study participation because the patients do not wish to continue, (3) missing more than 4 of 20 acupuncture treatment sessions, and (4) occurrence of a serious adverse event that the doctors consider should lead to termination of trial participation.

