### Statistical analysis

Before the data analyses, the research group will provide a statistical scheme to the statisticians. The scheme will include the required data and processing method. The data will be processed and analyzed by the statisticians by the scheme.

Intention-to-treat statistical analysis will be conducted. Missing data will be treated by imputation methods depending on the type: missing completely at random, missing at random, or not at random. Per-protocol analysis will include only patients who attended at least 80% of the sessions and completed the follow-up in the allocated intervention group.

Statistical analyses will be performed with SPSS 22.0 statistics software (IBM Corporation, Armonk, NY, USA). The data analysis process will be completed by statisticians who are independent of the research team and blinded to the test settings. A *t*-test and Wilcoxon test will be used to compare the numerical variables in the within-group analyses, including the WOMAC, VAS, AIMS2-SF, BAI, and BDI. Analysis of variance and the Kruskal-Wallis test will be used for numerical variables in the between-group analyses, including age, height, weight, scores of VAS, WOMAC, AIMS2-SF, BAI, BDI, and Credibility/Expectancy Questionnaire. The chi-squared test and one-way analysis of variance (ANOVA) will be used for categorical variables such as the demographic and baseline characteristics. The available data of the four groups (group A, group B, group C, and group D) will be tested by bilateral tests and the confidence intervals are all 95% bilateral, with a *P* value less than 0.05 being statistically significant.

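### Excluding patients from the study for unpermitted analgesics, interfering treatment or more than 4 missed sessions, with no continued assessment, undercuts the promised intention-to-treat analysis

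*Protocol article*

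**What the plan says.** Under Discontinuation criteria and modification, the protocol article states that "patients with KOA who meet the following criteria will be excluded from the study: (1) protocol violation such as taking analgesic without permission". Criterion (1) also covers "receiving additional treatment that may interfere with the efficacy of acupuncture". Criterion (3) is "missing more than 4 of 20 acupuncture treatment sessions". Criterion (2) is withdrawal of consent, and criterion (4) is a serious adverse event that the doctors judge should end participation.

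Under Statistical analysis, the article states: "Intention-to-treat statistical analysis will be conducted". The same section describes a second population: "Per-protocol analysis will include only patients who attended at least 80% of the sessions and completed the follow-up in the allocated intervention group".

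The primary outcome is the patient-reported WOMAC score at week 4. WOMAC at weeks 8 and 12 is secondary. The schedule (Table 1) has assessments at baseline and weeks 4, 8 and 12. Neither it nor the sections on outcomes, data collection or consent says that a patient excluded under criterion (1) or (3) is still assessed at those visits.

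**The concern.** Criteria (1) and (3) are events after randomisation. A patient with poor relief may take an analgesic without permission, seek other treatment or stop attending. A patient who improves early may also stop attending. In either case the event is plausibly related to the pain and function that WOMAC measures.

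Intention-to-treat compares everyone as randomised, whatever their adherence or co-treatment. If these patients leave the study when the event occurs, their later outcomes are not measured. The comparison then depends on values imputed for a group that the protocol itself removed. A later analysis plan can choose the imputation method, but it cannot recover scores that nobody collected.

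**Working it through.** **1. Attendance thresholds.** The inputs are 20 sessions, exclusion if more than 4 are missed, and per-protocol inclusion at 80% attendance or more.
- Criterion (3): missed ≥ 5, so attended ≤ 20 − 5 = 15.
- Per-protocol rule: attended ≥ 0.80 × 20 = 16.

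The ranges 0–15 and 16–20 do not overlap and leave no gap. Every patient who fails the per-protocol attendance rule is therefore one whom criterion (3) excludes from the study.

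**2. Timing against the primary outcome.** Treatment is 5 sessions a week for 4 weeks. If missed sessions are not made up later, the fifth miss can come as early as session 5 (end of week 1) and no later than session 20 (end of week 4). Criterion (3) is thus met by the end of the treatment period, and in many cases before the week-4 WOMAC. Criterion (1) can be met at any time in the trial. If it is met after week 4, only the week-8 and week-12 scores are at risk.

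**3. The plan's own allowance.** The Sample size section raises 45 to 50 per group for 10% loss in follow-up: 45 / (1 − 0.10) = 50, which reproduces. The margin is 50 − 45 = 5 patients per group. The section does not say whether it covers exclusions by rule. If loss and exclusion together came to 20% (an assumption), 50 × 0.80 = 40 per group would have observed outcomes.

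**4. Illustration of bias (assumed rates, no imputation).** The documents give no exclusion rates. Suppose that each arm loses a fraction p through a normally distributed tendency that correlates ρ with a worse outcome. The mean of the retained patients then improves by ρ·φ(c)/(1 − p) SD, where c is the normal quantile at 1 − p.
- p = 5%: φ(1.645)/0.95 = 0.1031/0.95 = 0.109
- p = 10%: 0.1755/0.90 = 0.195
- p = 20%: 0.2800/0.80 = 0.350
- p = 25%: 0.3178/0.75 = 0.424

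For an assumed true benefit of 0.60 SD:

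| Active excluded | Sham excluded | ρ | Apparent effect (SD) |
|---|---|---|---|
| 5% | 10% | 0.3 | 0.60 − 0.3 × (0.195 − 0.109) = 0.57 |
| 5% | 20% | 0.5 | 0.60 − 0.5 × (0.350 − 0.109) = 0.48 |
| 5% | 25% | 0.7 | 0.60 − 0.7 × (0.424 − 0.109) = 0.38 |
| 5% | 5% | any | 0.60 |
| 20% | 5% | 0.5 | 0.60 + 0.5 × (0.350 − 0.109) = 0.72 |

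The result can move either way or not at all. The table shows that selective exclusion can matter. It does not predict this trial's bias.

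**The case against.** The best defence is that exclusion from the study is not exclusion from the analysis. The section concerns discontinuation. The Statistical analysis section promises intention-to-treat with imputation, and a separate per-protocol set with an attendance cut makes sense only if the intention-to-treat set also holds lower attenders. The joint reading is that participation stops, later values are missing, and they are imputed. This reading is fair, and it rules out several stronger inferences that a reader might draw:

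- **That these patients leave the analysis, so the intention-to-treat set becomes the per-protocol set.** The document does not say so. The matching attendance cut alone does not make the sets equal, since the per-protocol set also requires completed follow-up in the allocated group.
- **That the missing-data method is chosen after seeing the data.** The text says "Missing data will be treated by imputation methods depending on the type: missing completely at random, missing at random, or not at random", but the same section has a statistical scheme, including the processing method, supplied before the analyses. Details of imputation may be left to an analysis plan.
- **That "The available data of the four groups" defines a complete-case analysis.** The phrase opens a sentence on two-sided tests and confidence intervals. It is loose wording, not a population definition.
- **That the sham arm must lose more patients, or that the primary outcome is always lost.** Participants are blinded, missed sessions may follow improvement, and exclusion after week 4 leaves the primary outcome intact.

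The article also condenses a fuller protocol, which may provide for continued assessment. The point rests on what is printed, however: a rule that ends study participation for non-adherence, alongside an intention-to-treat promise. Even on the defence's reading, the outcomes after exclusion are uncollected and must be imputed.

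**Conclusion.** The point holds as a conflict between trial conduct and analysis. Criteria (1) and (3) end study participation for reasons plausibly related to outcome, and no section keeps these patients under assessment. The intention-to-treat analysis would therefore rest, for them, on imputed values, including week-4 WOMAC when exclusion comes earlier. The overlap of criterion (3) with the per-protocol attendance rule is exact (15 or fewer against 16 or more of 20).

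The size and direction of any bias cannot be derived from the document. The shifts shown, from 0.60 SD to between 0.38 and 0.72 SD, rest on assumed exclusion rates and correlations, an assumed true effect, and no imputation. The conflict does not depend on them.

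**What to change.** Reconcile the discontinuation criteria with the Statistical analysis section. For criteria (1) and (3) only, state that:

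- the event is recorded as a protocol deviation;
- the patient continues to be assessed at the scheduled weeks 4, 8 and 12 unless consent to follow-up is withdrawn;
- the patient is analysed in the group to which he or she was randomised;
- the criteria serve only to define the per-protocol set. The printed definition covers attendance and follow-up but not criterion (1), so criterion (1) would be added to it.

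Leave criterion (2) (consent) and criterion (4) (serious adverse events) as they are. The change should therefore not be made in the lead-in sentence, which governs all four criteria. The clinical rules on analgesics and additional treatment, and whether trial treatment continues after such an event, are not addressed here. The choice of model and missing-data method can stay with the analysis plan. If the full protocol already keeps these patients under assessment, only the published wording needs to be aligned.

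The cost is a short amendment and a few extra assessments at visits already in the schedule.

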### Informed consent

Each patient will be informed of the study protocol information regarding random allocation, possible benefits and risks, and so on. Then, we will provide sufficient time for all patients to decide whether to participate in the trial. Only if they voluntarily sign the informed consent will they be randomized to a group. Moreover, the patients will be free to withdraw from the study at any time without a specific reason and any penalty or loss of benefits. However, we will attempt to record the reason for withdrawal and encourage the participant to remain in the study if possible.

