### Safety assessment

Adverse events (AEs) caused by acupuncture such as pain, bleeding, fainting, allergy, or other severe events will be processed immediately and recorded in detail in the case report forms (CRF). Participants with mild and moderate AEs will be treated for their symptoms and closely monitored as necessary by the researcher, while severe AEs will be reported to the Research Ethics Committee, which will provide medical advice to the research team within 48 h, and the Research Ethics Committee will determine whether a termination of the trial is required. Patients may choose to withdraw from the trial due to any AE.

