### Data collecting and monitoring

The governance of this study will be carried out by the trial steering committee (TSC), composed of the primary investigators and statisticians, who will oversee the entire study conduct to ensure that all researchers participating in this study are following the proposed protocol. A monthly meeting will be conducted where the TSC can supervise the progress and the data quality of this study and share suggestions if problems occur. The Ethics Committee will hold an annual meeting to monitor the implementation of the entire trial.

In this study, the data that includes observation time points, scanning time points, outcome measures, adverse events, and safety evaluations will be collected at baseline and weeks 4, 8, and 12 after the intervention using the case report form. And a special assistant will be responsible for reviewing data integrity, accuracy, and consistency. Patients will be assigned to a quiet room for psychological factor assessments. In order to ensure the consistency of source data, all the scales will be assessed by the same researcher during the study. Meanwhile, the research data will be input into EpiData electronic database. For ensuring the accuracy of data entry, data will be entered independently by two researchers, and then the discordances will be resolved by tracing source data.

When the trial is completed, the database will be locked by the data management team, after which the researchers can no longer modify the data. Both paper files and electronic documents will be preserved for at least 5 years after publication. If readers and reviewers have any questions, they can contact the corresponding author for access to the original data. Patient information will remain anonymous, including name, ID number, and telephone number.

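### Discontinuation criterion (4) names exclusion from the study as the only consequence of a participation-ending serious adverse event and does not separate stopping acupuncture from stopping assessment

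*Protocol article*

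**What the plan says.** All references are to the protocol article.

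- **Discontinuation criteria and modification.** The lead-in, which covers the whole trial period, states that "patients with KOA who meet the following criteria will be excluded from the study". Criterion (4) is "occurrence of a serious adverse event that the doctors consider should lead to termination of trial participation". Withdrawal of consent is a separate ground, criterion (2): "withdrawal of consent for study participation because the patients do not wish to continue".
- **Study design.** "The treatment procedure will include 20 sessions of treatments in total from baseline to week 4 and 2 times of follow-ups", the latter at weeks 8 and 12. Treatment is therefore finished by week 4, while the trial continues to week 12.
- **Table 1, note.** "The evaluation will be performed at baseline and weeks 4, 8, and 12 respectively after randomization". The table also marks adverse events through to week 12.
- **Data collecting and monitoring.** "adverse events, and safety evaluations will be collected at baseline and weeks 4, 8, and 12 after the intervention using the case report form".
- **Safety assessment.** Adverse events caused by acupuncture are written up in the case report form, and "severe AEs will be reported to the Research Ethics Committee, which will provide medical advice to the research team within 48 h".
- **Informed consent.** For patients who choose to leave, "we will attempt to record the reason for withdrawal and encourage the participant to remain in the study if possible".
- **Statistical analysis.** The plan is intention-to-treat, with imputation chosen by the presumed type of missingness. A separate per-protocol set is defined by attendance of 80% or more of the sessions and a finished follow-up.

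**The concern.** Consent withdrawal has its own criterion, so criterion (4) reaches patients who are still willing to be assessed. Both the lead-in and the criterion speak of the study or the trial, not of the treatment. The section offers no middle course in which needling stops and assessment continues, and Safety assessment does not supply one.

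What is at stake is completeness of data. An intention-to-treat analysis is best served by observed outcomes in everyone randomised, including those who stopped treatment early. If exclusion follows the text, obtainable WOMAC scores become missing ones, and the week 4 primary value is among them when exclusion comes before that visit. Imputation would then replace measurements that could have been made. Later adverse-event follow-up would also end in a patient who has just had a serious event.

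The exclusion is not needed for the per-protocol analysis, because that set already has its own definition. It also fits poorly with Informed consent: a patient who wants to leave is encouraged to stay, while one who may want to stay is removed.

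**Working it through.** The plan gives no figure on this point, so the check is a reading of the text followed by a count from Table 1.

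**Step 1: what the text requires.**

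- Trigger: a serious adverse event and a judgement by the doctors that participation should end.
- Consequence: exclusion from the study. No other consequence is named.
- Consent: a separate criterion, so it need not have been withdrawn.
- Follow-up after exclusion: no section says that it continues. The loss of later visits is an inference, but it is the plain meaning of being excluded from a study.

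**Step 2: scheduled data per patient (Table 1).**

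- Outcome scales after baseline: WOMAC, VAS, AIMS2-SF, BAI and BDI, at weeks 4, 8 and 12. 5 × 3 = 15 assessments.
- Adverse-event time points after baseline: weeks 1, 2, 3, 4, 8 and 12, so 6.

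**Step 3: data lost by time of exclusion.** Lost outcome assessments = 5 × number of visits remaining.

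| Exclusion | Outcome assessments lost | Adverse-event time points lost | Primary WOMAC lost |
|---|---|---|---|
| Before the week 4 visit | 5 × 3 = 15 of 15 | 3 to 6 of 6 | Yes |
| Between weeks 4 and 8 | 5 × 2 = 10 of 15 | 2 of 6 | No |
| Between weeks 8 and 12 | 5 × 1 = 5 of 15 | 1 of 6 | No |

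Before week 4 the adverse-event loss is 6 of 6 if exclusion comes before week 1, 5 between weeks 1 and 2, 4 between weeks 2 and 3, and 3 between weeks 3 and 4.

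**Step 4: patients affected.**

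- One patient per arm: 1/50 = 2%.
- The document gives no rate of serious events. Assumption: 0 to 2 such patients per arm. Over 4 arms that is 0 to 8, and 8/200 = 4%, so the range is 0% to 4%.
- For comparison, the Sample size section allows 10% loss: 45/(1 − 0.10) = 50, or 5 patients per arm. The assumed 0 to 2 per arm would fit inside that allowance if other losses leave room.

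**Step 5: interaction with criterion (3).** That criterion excludes patients who miss more than 4 of 20 sessions, that is, 5 or more. Three weeks at 5 sessions per week is 15 sessions. A patient whose acupuncture stops at or before session 15 therefore misses at least 20 − 15 = 5 and would also meet criterion (3). Rewording criterion (4) alone would not keep that patient in follow-up.

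**The case against.** The strongest reply is that criterion (4) is discretionary. It applies only when the doctors conclude that participation should end, and a doctor who thinks that only the needling should stop is not told to invoke it. If participation is read to include assessment, the doctors have in effect decided that assessment should end too. This stands in part: a medical judgement comes before any loss, so it would be too strong to say that the rule by itself creates missing data. What remains is that the text gives the doctors only one stated outcome and does not ask them to consider treatment and assessment separately.

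Second, the section concerns discontinuation and does not mention visits, and a journal article condenses the full protocol. This is a fair caution about an inference. It does not remove the point, because the article states a consequence and that consequence is worded as exclusion from the study. If treatment alone was meant, the same rewording is needed.

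Third, a reader might infer that these patients drop out of the intention-to-treat analysis, so that the plan contradicts itself. The documents do not support that. Nothing under Statistical analysis removes them from the set, and imputation is provided for. The tension is with data completeness, not with the definition of the population.

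Fourth, a reader might infer that the serious event goes unrecorded. That is not supported either. Safety assessment has acupuncture-caused events entered in the case report form and severe ones sent to the ethics committee. The criterion says serious and that section says severe, and the two are not treated as the same here. What may be lost is later follow-up, not the event.

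Finally, criteria (1) and (3) share the lead-in, are not conditional on a doctor's judgement, and would probably affect more patients. That is so, but it does not repair criterion (4).

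**Conclusion.** The point holds as a minor weakness in wording. Criterion (4) ties a participation-ending serious adverse event to exclusion from the study and provides no route by which a consenting patient stops acupuncture but stays under assessment. Read plainly, that patient loses 5 to 15 of the 15 scheduled outcome assessments, including the primary WOMAC if exclusion comes before the week 4 visit.

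The expected effect on the trial is small: 0% to 4% of patients under an assumed 0 to 2 per arm, a range that includes none. The conclusion rests on the plain reading of exclusion from the study and on the doctors invoking the criterion. No direction of bias between arms can be claimed, because the document gives neither event rates nor any reason to expect them to differ by arm.

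**What to change.** Reword criterion (4) along these lines: a serious adverse event that the doctors judge incompatible with further treatment ends acupuncture only. The patient stays in the scheduled week 4, 8 and 12 outcome and adverse-event assessments, the outcome of the event is recorded, and the patient is analysed as randomised. There are two exceptions: consent is withdrawn (criterion 2), or the doctors judge the assessments themselves unsafe. An event after week 4, when no study treatment is left to stop, changes nothing in the assessment schedule.

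Add a clause that sessions missed because of such an event do not trigger exclusion under criterion (3). Otherwise a patient who stops at or before session 15 is removed by that route. The per-protocol set can stay as defined.

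The cost is one reworded criterion with that clause, and at most the already scheduled visits of a few patients. The downside is continued contact with a few patients who are off treatment.
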